### Termination and withdrawal criteria

2.9

All participants will be notified of their right to stop treatment and withdrawal from the study on any grounds at any time, and the reason for withdrawal will be documented in the case report form (CRF). They will get standardized treatment if they withdraw. The following criteria are used to stop treatment and withdraw from the study project:

1.Patients with severe allergies to the study drug in the course of treatment cannot continue to participate in the clinical study.2.The participant has poor compliance or is taking other medications prohibited by this study protocol.3.Loss of follow-up or voluntary withdrawal from the trial.

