### Compliance

3.4

Upon randomization of participants, investigators at the study site will use all reasonable efforts to follow up with participants throughout the study. Adherence to the intervention will be monitored on each visit, and participants will be required to have all study containers returned with any unused granule packets, including all empty containers. Messages will be sent prior to each visit via WeChat or phone to remind participants of the impending data collection. Furthermore, ongoing support will be offered to participants during the follow-up phase, including free registration and treatment counselling.

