### Statistical analysis

3.7

The intention to treat principle will be followed for all data analysis. The Statistical Package for the Social Sciences version 22.0 (SPSS 22.0, Chicago, IL) will be used to analyze the data. The analysis method should be based on the characteristics of the data distribution: The measurement data will be expressed as mean ± standard deviation and normal distribution, paired *t* test will be used for comparison before and after treatment, *t* test will be used for between-group comparisons (homogeneity test of variance will be performed with 0.05 as the test standard), and rank sum test will be used for comparison between groups. Chi-square test will be used for enumeration data, and rank-sum test will be used for grading data. Bilateral tests will be used for all tests, with *P* < .05 indicating a significant difference. For baseline data, the full analysis set (FAS, including completed cases and dropout cases, excluding censored cases) is used, and the full analysis set and the per-protocol set(PP set, including completed cases, excluding dropout cases and censored cases) are used for efficacy evaluation, which can enhance the reliability of trial results when the conclusions of the two analyses are consistent. When inconsistencies arise, differences should be fully discussed and explained. In the analysis of the full analysis set, the missing data are substituted by the method of sequence mean value.

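### If missing values are filled with a mean across participants, agreement of the full analysis and per-protocol sets at month 18 cannot reveal informative dropout and is not evidence of reliability

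*Protocol article*

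**What the plan says.** Section 3.7 (Statistical analysis) uses two sets for efficacy and does not say which one decides.

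- The full analysis set is defined as "FAS, including completed cases and dropout cases, excluding censored cases".
- The per-protocol (PP) set is defined as "PP set, including completed cases, excluding dropout cases and censored cases".
- For missing values: "In the analysis of the full analysis set, the missing data are substituted by the method of sequence mean value". Whether the mean is taken over all participants, within arm, or over a participant's own visits is not stated.
- On using both sets: "which can enhance the reliability of trial results when the conclusions of the two analyses are consistent". Inconsistent conclusions are to be discussed and explained.

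Two other sections bear on the PP set. Section 2.9 lists among its grounds for stopping treatment and withdrawing: "The participant has poor compliance or is taking other medications prohibited by this study protocol". Section 3.4 provides for adherence checks at every visit, based on what is brought back: "participants will be required to have all study containers returned with any unused granule packets". Treatment lasts 6 months and follow-up a further 12 (sections 2.1 and 3.1). Section 2.4 bases the sample size on FEV1 at 18 months.

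**The concern.** Comparing two analysis sets is informative only if they can differ when something is wrong. Here the FAS is the PP set plus the dropouts. A participant who has left has no month-18 FEV1, so at that visit the extra FAS rows are filled values. If the fill is a mean of other participants, it is computed from the same people who make up the PP set. The FAS result is then a transformation of the PP result.

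What the comparison ought to expose is dropout related to outcome. If experimental-arm participants who leave are doing worse, completers flatter the treatment, and so does an FAS filled from completers. The two would agree, and the plan would count that agreement in the result's favour.

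A second, smaller matter is what the PP set represents. Its definition turns on completion and states no adherence criterion of its own. A participant who took all 6 months of granules and was lost at month 15 is excluded.

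**Working it through.** **Inputs.** From section 2.4: means 2.54 and 2.83, SDs 0.65 and 0.73, 121 per group before dropout, 10% dropout, 135 per group enrolled. From section 3.7: two-sided 0.05, t test between groups. Dropout of 20% is an assumption, added to show the trend.

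**The plan's own figure.** Common SD = √[(0.65² + 0.73²)/2] = √0.4777 = 0.691; difference = 0.29. Power is not stated. Assuming 90%, n = 2 × 0.4777 × (1.960 + 1.282)²/0.29² ≈ 119.4, so 120 per group against the stated 121. Then 121/0.9 = 134.4, so 135. The planning figures reproduce.

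**PP set at month 18, 10% dropout.** Completers per arm = 135 × 0.9 = 121.5. SE = 0.691 × √(2/121.5) = 0.0887; t = 0.29/0.0887 = 3.27.

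**FAS, pooled mean.** With dropout share d in each arm:

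- Difference = (1 − d) × 0.29 = 0.261 at 10% and 0.232 at 20%.
- Within-arm variance = (1 − d)s² + d(1 − d)(0.29/2)². At 10%: 0.4299 + 0.0019 = 0.4318, SD 0.657.
- SE = 0.657 × √(2/135) = 0.0800; t = 0.261/0.0800 = 3.26.

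The t statistic hardly moves (3.26 against 3.27) while the estimate falls by a tenth.

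**FAS, arm mean.** The difference stays at 0.29. SD = √(0.9 × 0.4777) = 0.656; SE = 0.656 × √(2/135) = 0.0798; t = 3.63, which is the PP value divided by 0.9. With no true effect, the FAS therefore rejects when the PP statistic exceeds 1.96 × 0.9 = 1.764, a two-sided probability of 7.8%. At 20% dropout the cut-off is 1.568 and the probability 11.7%.

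**Simulation.** 4,000 trials per scenario, 135 per arm, month 18. Type I error with arm means and random dropout was 7.6% at 10% and 11.8% at 20%. With pooled means, the FAS and PP verdicts differed in 0.0–0.2% of trials in every scenario, including informative dropout.

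The next table asks whether disagreement responds to informative dropout. Assumptions: effect 0.20 among completers, 10% dropout per arm and, in the last column, experimental-arm dropouts worse by 0.5. The own-visits row assumes a correlation of 0.9.

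| FAS value for dropouts | FAS and PP disagree, random dropout | Disagree, informative dropout |
|---|---|---|
| Pooled mean | 0.1% | under 0.1% |
| Arm mean | 6.9% | 7.0% |
| Mean of own visits | 11.2% | 29.1% |
| True month-18 value | 11.0% | 20.1% |

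Using the dropouts' true values, the difference falls from 0.200 to 0.149, and disagreement rises from 11.0% to 20.1%. Under either across-participant mean, the rate does not change when dropout becomes informative. The disagreement under arm means comes from overstated precision in the FAS, not from any signal about dropouts.

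**The case against.** **Adherence does enter the PP set.** A reader might infer that the PP set ignores adherence altogether. Section 2.9 does not support that: poor compliance and prohibited medication are grounds for withdrawal, and a withdrawn participant leaves the PP set. The packet returns in section 3.4 may well inform that judgement. What stands is narrower. The PP definition has no criterion of its own, section 2.9 gives no threshold, and neither helps the adherent participant lost during follow-up. A numerical threshold is detail that an analysis plan could supply, so its absence carries little weight here.

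**Agreement is not built in under every reading.** This is correct. With a mean of the participant's own visits, the verdicts differed in 3–17% of simulated trials under random dropout and 29–45% under informative dropout. With arm means they differed in 2.6–7% at 10% dropout and up to about 15% at 20%. The text does not settle which mean applies, so the point is conditional.

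**The sets do not share all their real data.** Also correct for part of the schedule. Section 3.2 measures FEV1 at seven visits. Before a participant drops out, the FAS holds observed values that the PP set lacks, and comparing the sets there carries some information.

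**The agreement sentence is mild.** It says agreement can add reliability, the section opens with the intention-to-treat principle, and inconsistencies are to be explained. No text says that agreement confirms a result. Even the mild claim is unsupported at month 18 under an across-participant mean.

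**Conclusion.** The point holds in a conditional form. If the sequence mean is taken across participants, the FAS adds nothing about dropouts at month 18, so its agreement with the PP set cannot detect informative dropout. A pooled mean shrinks the planned effect by the dropout share (0.29 to about 0.26 L at 10%, 0.23 L at 20%) and returns the PP verdict essentially always. An arm mean returns the PP estimate with false precision: type I error about 7.6% at 10% dropout and 11–12% at 20%. These sizes rest on the section 2.4 means and SDs, equal dropout in the arms and, for type I error, random dropout. The point fails for an own-visits mean and at visits before dropout.

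A reader might also infer a large false-positive risk. Simulations with no true effect can give both sets falsely significant in about 20% of trials at 10% dropout and 46% at 20%. That scenario has experimental-arm dropouts about 0.9 L below completers, roughly three times the planned 0.29 L, with random dropout among controls. Nothing in the protocol supports an assumption that extreme, and those rates come from the assumed dropout pattern rather than from the PP definition or the agreement sentence. They should not be read as the expected size of the problem.

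**What to change.** In section 3.7:

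1. Name the FAS as the deciding efficacy analysis. Analyse it with a repeated-measures model on all observed visits, and delete the mean filling. This removes both the shrinkage and the false precision, and uses the dropouts' real data from earlier visits.
2. Replace the sentence on agreement of the two sets with a pre-specified missing-not-at-random sensitivity analysis, for example a range of assumed shifts in dropouts' FEV1 by arm. That addresses directly what the comparison of sets cannot.
3. Define the PP set by treatment received, with a pre-set share of packets taken according to the returns already collected under section 3.4, rather than by completing month 18. State what a censored case is.

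The cost is wording and modest programming, with no new data collection. The PP set may change in size, since late losses with good adherence would enter and completers below the pre-set share would leave.

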### Sample size

2.4

The sample size was calculated on the primary outcome (the forced expiratory volume in 1 second (FEV1) at 18 months). According to the previous literature,^[10]^**t**he mean value of FEV1 in the control group is estimated to be 2.54 with a standard deviation of 0.65. After the herbal treatment the mean value of FEV1 in the experimental group is 2.83 with a standard deviation of 0.73. The calculation of the sample size for the experimental and control groups of each was 121 cases using the software Power Analysis and Sample Size version 11.0 (PASS 11.0). Altogether, 268 participants are recruited at a 10% dropout rate. For the actual study, 135 cases per group will be included.

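### Filling missing FEV1 with the series mean either shrinks the treatment effect or understates its standard error, and ignores the patient's own earlier values

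*Protocol article*

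**What the plan says.** The missing-data rule is in section 3.7 (Statistical analysis) of the protocol article. For the full analysis set, "the missing data are substituted by the method of sequence mean value". The same section defines that set as "including completed cases and dropout cases, excluding censored cases", so patients who leave early enter the efficacy comparison through imputed values. It also states that "The intention to treat principle will be followed for all data analysis", names SPSS 22.0, and compares groups by a two-sample t test at two-sided 0.05. Efficacy is also analysed in a per-protocol set without dropouts, and agreement of the two sets is taken as added reliability.

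Section 3.2 measures the primary outcome, post-bronchodilator FEV1, at 1, 3, 6, 9, 12, 15 and 18 months. Section 2.4 sizes the trial on the 18-month value and expects dropout: "Altogether, 268 participants are recruited at a 10% dropout rate".

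The text does not say whether the mean is pooled or taken within arm. It gives no role to a patient's baseline or earlier visits in filling a gap.

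**The concern.** Mean substitution goes wrong in one of two ways, depending on how the mean is taken.

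- **Pooled over arms.** Dropouts in both arms receive the same value, so the estimated difference shrinks by the dropout share.
- **Within arm.** The imputed values add no variance, yet each counts as an observed patient, so the standard error is too small.

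Both versions discard the best available information. A patient's FEV1 at month 15 says far more about month 18 than a group average does when the between-patient SD is 0.65 to 0.73. Both also place every dropout at the average, so dropout among patients who are doing badly becomes invisible. The rule governs the intention-to-treat comparison of the primary outcome, so the headline estimate, its interval or its p value is affected.

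**Working it through.** **Inputs from section 2.4:** means 2.54 (SD 0.65) and 2.83 (SD 0.73), so the difference is δ = 0.29; 121 per group before dropout; dropout d = 10%; 135 enrolled per group. No unit is printed; litres are assumed.

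**The plan's own figure.** Average SD = √((0.65² + 0.73²)/2) = 0.691. At two-sided 0.05 and 90% power the normal formula gives 120 per group, and the t test first passes 90% at 121 (90.2%). The article does not state power; 90% is inferred, since 80% gives 90 per group and 85% gives 102. Then 121/0.9 = 134.4, or 268.9 in total. The planning figures reproduce.

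**Pooled mean, random dropout.** Each arm mean becomes (1−d) × its observed mean + d × the common mean. The common part cancels, so the expected difference is (1−d)δ = 0.9 × 0.29 = 0.261.

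**Within-arm mean, random dropout.** The sum of squares comes only from observed patients but is divided by the full n, so the estimated variance is about (1−d)σ².
- Full-data standard error: √((0.65² + 0.73²)/135) = 0.0841.
- Reported: 0.0841 × √0.9 = 0.080.
- True: 0.0841/√0.9 = 0.089.
- Ratio: 1−d = 0.9.
- Type I error: 2 × (1 − Φ(1.96 × 0.9)) = 2 × (1 − Φ(1.764)) = 7.8%.

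**Range over dropout.** Only 10% is in the protocol; the other rates are assumptions.

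| Dropout | Pooled mean: expected difference (true 0.29) | Within-arm mean: type I error |
|---|---|---|
| 5% | 0.276 | 6.3% |
| 10% | 0.261 | 7.8% |
| 15% | 0.247 | 9.6% |
| 20% | 0.232 | 11.7% |
| 30% | 0.203 | 17.0% |

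**Simulation** (20,000 trials, 135 per arm, 10% random dropout):
- Pooled: estimate 0.259, 95% interval coverage 93.4%, type I error 5.3%.
- Within arm: estimate 0.289, reported standard error 0.0795 against a true 0.089, coverage about 92%, type I error 8.1%.

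**Information discarded.** The RMS error of a value set to the mean is about 0.69. Predicted from the patient's own earlier FEV1 it would be 0.691 × √(1 − r²): 0.41 at r = 0.8 and 0.30 at r = 0.9. These correlations are assumptions.

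**Dropout related to FEV1** (assumed mechanisms).
- If 10% of controls leave with FEV1 0.5 L below their peers, this contributes 0.1 × 0.5 = 0.05 L to the true difference. Mean substitution reduces that contribution to 0.00.
- Suppose control dropout depends on baseline FEV1, treated dropout is random, about 10% is missing, and the baseline–outcome correlation is 0.7 to 0.9 (4,000 trials, true difference 0.29):

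| Method | Estimate | Type I error |
|---|---|---|
| Pooled mean | 0.213–0.222 | 7.1–9.7% |
| Within-arm mean | 0.236–0.247 | 10.4–13.4% |
| Baseline-adjusted, observed data | 0.291–0.294 | 4.7–4.9% |

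**The case against.** - **Under the pooled reading the test is nearly valid.** With random dropout the difference and its standard error shrink together: 0.261/0.080 and 0.29/0.089 are both about 3.3. Type I error stays near 5% and power equals that of complete cases, about 90%. This stands. On that reading the damage is to the estimate and its interval, and the 7.8% belongs only to the within-arm reading. But the article does not say which applies, and neither is sound.
- **The term is undefined.** It could mean the average of a patient's own visits. The figures above would then not apply, nor would the point about ignoring earlier FEV1. That reading is strained for SPSS, and it would still be a single filled-in value treated as observed.
- **Neither analysis set is ranked, and the per-protocol set contains no imputed dropouts.** True, but the intention-to-treat statement makes the full analysis set the natural lead. The per-protocol set deletes dropouts, so it cannot reveal informative dropout. Under within-arm substitution the estimate at a visit equals the observed-case difference, so agreement between the sets is largely built in.
- **The larger effects rest on assumptions.** This also stands: dropout above 10%, the correlations and the dropout mechanisms are not in the document.
- **The mixed model is not the only cure.** Multiple imputation using earlier visits, followed by the planned test, would also work. The mixed model recovers an informative loss only as far as observed FEV1 explains it, which is why a sensitivity analysis is needed too.

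**Conclusion.** The concern holds. The protocol fixes an unsound rule; this is not a detail left for a later analysis plan. At the planned 10% dropout, completely at random, it costs either 0.029 L of a 0.29 L effect (pooled) or about 3 percentage points of type I error (within arm). That is moderate. Both harms grow with the dropout share. If dropout is related to FEV1, they can be larger, by an amount that depends on mechanisms the document does not give. All figures assume that the mean is taken across patients. Because the rule governs the intention-to-treat analysis of the primary outcome and is cheap to replace, it should be changed before unblinding.

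**What to change.** Delete mean substitution from section 3.7. State instead that FEV1 will be analysed from all observed visits with a likelihood-based mixed model for repeated measures, with baseline FEV1, visit, treatment and treatment-by-visit terms, and with the month-18 contrast reported. This is valid under missing at random and uses each patient's earlier values. Add one sensitivity analysis for informative dropout, by delta-adjusted or reference-based multiple imputation.

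The cost is one replaced sentence on missing data and a matching change to the between-group test named for FEV1, plus somewhat more analysis work. The model runs in SPSS MIXED or in SAS. The visits are already scheduled, and the planned 135 per group need not change.

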## Discussion

4

In China, COPD is a common chronic respiratory disease, and the present situation on the prevention and control of this chronic disease is not optimistic. Characterized by high morbidity, mortality, and disease burden, COPD has emerged as one of the most salient public and medical problems.^[14]^ Although modern medicine has been very effective in alleviating the symptoms of COPD, these measures cannot fully control disease progression and prevent acute exacerbations. New interventions are still needed to improve efficacy.^[15]^ TCM has long been extensively used in the treatment of COPD in China due to its low probability of adverse effects and low cost.^[16]^ With a history of use of several hundred years, Modified Shenling Baizhu Powder is a commonly used formula for the treatment of stable COPD.

But to date, the efficacy and safety of Modified Shenling Baizhu Powder in early-stage COPD has rarely been uniformly understood. Therefore, a prospective and convincing trial is necessary to demonstrate the risks and benefits of adding Modified Shenling Baizhu Powder to the therapy of participants with COPD based on syndrome differentiation. As far as we know, it is the first clinical trial to investigate the effectiveness of Modified Shenling Baizhu Powder with Western medicine in the delaying of early-stage COPD (GOLD stage I–II) lung function deterioration. We will focus on lung function, CTA, mMRC, SGRQ, quality of life, and safety in both treatment and follow-up phases. In our trail, we will use effective objective tools like lung function tests, which improve the reliability and generalizability of the results.

The study has some limitations. First, since the study was conducted in Sichuan, China, the relative effects of the test drugs are unclear whether they would be comparable among other ethnic groups. Second, in clinical practice, participants with pure COPD are rare and most of them are associated with other diseases such as hypertension, diabetes, and coronary heart disease. Therefore, the utility (extrapolation) of the results of this study is unclear and requires further evaluation. That said, the results shall aid the decision-making process for COPD therapy and management as well as provide important information which could be incorporated into guidelines for future treatment. A multicenter randomized controlled trial should be conducted in the future, to investigate a large sample of COPD participants and implement a multidimensional comprehensive evaluation.
